### Randomization

A listing of Melbourne suburban primary schools (n = 367), their enrolment number and associated suburb socioeconomic index for areas (SEIFA) score (suburb disadvantage score) will be obtained. Schools with an enrolment of over 300 students will be grouped in quintiles of SEIFA score and schools from the first, third and fifth quintiles will be selected to represent low, mid and high SEIFA strata respectively. Schools in each stratum will be randomly ordered with probabilistic weighting according to enrolment number, and will be approached consecutively and offered participation. Schools will then be randomly allocated to either SB-I, PA-I, SB+PA-I or current practice control (C).

## Intervention

### Development and Pilot Phase

A previous research-to-practice study (Switch-2-Activity) demonstrated the feasibility of teachers delivering materials targeting the promotion of children's physical activity and reductions in screen time [49]. For the current study, seven teachers, including a vice-principal, were interviewed regarding the feasibility of introducing regular classroom standing breaks. Short breaks were considered feasible with consistent feedback regarding the duration; anything longer than 2-minutes was viewed as being unlikely to be adopted by teachers. A subsequent pilot study to assess the feasibility and effectiveness of regular 2-minute classroom breaks found a 20-minute decline in children's objectively measured sedentary time during class and a corresponding 20-minute increase in moderate- to vigorous-intensity physical activity [50]. All class-based components of Transform-Us! were developed by the investigators with input from current and previous primary schools and representatives of the Victorian Department of Education and Early Childhood Development.

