### Aims

The primary aim of the Transform-Us! study is to determine whether an 18-month, behavioral and environmental intervention in the school and family settings results in higher levels of physical activity and lower rates of sedentary behavior among 8-9 year old children compared with usual practice (post-intervention and 12-months follow-up). The secondary aims are to determine the independent and combined effects of PA and SB on children's cardio-metabolic health risk factors; identify the factors that mediate the success of the intervention; and determine whether the intervention is cost-effective.

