### Sample size calculations

It is expected that the intervention effects on behavioral and biological primary outcomes will be moderate in size (standardized difference ~ 0.32, equivalent to a mean change in objectively-measured PA of 8 minutes per day [SD = 18 min] and a change in body mass index (BMI) units (age-sex difference from population norm data) of 1.9 kg/m^2 ^[SD = 0.25]) [25,46]. Without accounting for school cluster effects, the number of participants needed to detect a standardized difference of 0.32 with 0.8 power for sedentary behavior (SB-I) and physical activity (PA-I) alone and in combination (SB+PA-I), using a significance level of 0.05 with a two-tailed test, assuming a retention rate of 91% (based on the team's previous experience) and 20 participating schools, would be 340 in total (17 per school). With a previously observed school clustering effect of 0.018 (intra-class correlations [ICCs] for sedentary behavior, physical activity and BMI outcomes estimated using data from a previous intervention study)[44], the minimal total number of participants needed is 520, i.e., 26 per school. Hence, we will conservatively recruit 30 participants per school, giving a total sample size of 600 participants.

Moderate mediated effects of the intervention on the behavioral outcomes are expected (here a moderate mediated effect size is defined as standardized regression coefficients α and β of ~ 0.39)[47]. According to a 2007 simulation study by Fritz and MacKinnon [48], to detect a moderate mediated effect size with 0.8 power, using a significance level of 0.05 with a two-tailed test and bias-corrected bootstrap methods, ~ 61 independent observations are needed. If we assume a 9% rate of loss to follow-up, an average school cluster effect of 0.03 for the mediators (ICCs estimated using data from a previous intervention study)[44] and an average of 30 observations per school (see above), the sample size needed to detect a moderate mediated effect size would be 100 (20 per school). Hence, the sample size needed to detect moderate intervention effect sizes with 0.8 power for the primary outcomes (n = 600) will also be sufficient to detect a moderate-sized effect with 0.8 power for the mediating variables.

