#### Interrupting classroom sitting time

Teachers will modify the delivery of one class lesson per day (~30 minutes) so that children will complete the lesson standing up. Teachers will be provided with a suite of standing lesson delivery methods that can be modified to any class topic (e.g., 'Stations around the room' shown in Appendix 1). If administered as intended, this should result in approximately 150-minutes less sitting time per week. In addition, every two-hour classroom teaching block will be interrupted every 30 minutes with a 2-minute guided light-intensity activity break (e.g., 'Bean-bag Spelling/counting' shown in Appendix 2). This will equate to a total of six minutes interrupted sitting time every two hours. On average, schools in Victoria have two 2-hour teaching blocks per day so this should result in up to 60-minutes less sitting time per week. Teachers will be provided with a menu of activities to deliver during the 2-minute breaks.

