### Combined sedentary behavior and physical activity intervention arm (SB+PA-I)

Schools randomized to the combined SB+PA-I intervention arm will receive a blended version of the two interventions, but with the same intervention 'dose'. For example, when children in this arm complete a behavioral contract to switch off the television, they will be encouraged to participate in physical activity (SB-I children will not be directly encouraged to participate in activity when they switch off their television). The combined intervention arm will include 18 class lessons (9 per year), standing lessons and interruptions to children's classroom sitting time (short breaks), the promotion of physical activity during recess and lunch breaks, and 18 newsletters to parents.

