### Data analysis

All statistical analyses will be performed using Stata 9.1 for Windows (StataCorp LP) and will adjust for clustering by observations by school (the unit of randomization). All analyses will be conducted using the intention to treat principle. Generalized Estimating Equations (GEE) [84] will be used to fit regression models to describe the effects of the intervention on key outcome variables among children. Separate models will be fitted to determine differences in key outcome variables in the intervention and control groups.

Separate models will be evaluated for each assessment point (mid-intervention; post-intervention; 12 months follow-up), adjusting for baseline levels of the outcome, and, where appropriate, baseline levels of the mediating variables. PA-I and SB-I intervention conditions will be the predictors of primary interest (entered in the form of two indicator variables and their interaction term). Analyses will be performed excluding and including children who were recruited to the study after baseline. For physical activity outcomes, we will compare the PA-I and SB+PA-I versus the SB-I and C groups. For sedentary behavior outcomes, we will compare SB-I and SB+PA-I versus the PA-I and C groups. For health outcomes, we will compare C versus the other three groups and the SB+PA-I versus the single intervention groups. All models will be adjusted for measured confounders. As it has been argued that adjustment for multiple comparisons should not be used when assessing evidence about specific hypotheses no adjustment for multiple comparisons will be performed [85]. To evaluate the magnitude and direction of the intervention effects mediated by intrapersonal, interpersonal and environmental processes, the product-of-coefficient method will be used [86]. A first set of GEE regression models will assess the impact of the intervention condition (regression coefficient α) on the residualized change score of the hypothesized mediators (Table 1), after controlling for significant covariates. A second set of GEE regression models will estimate the independent effects of the intervention condition and residualized changes in the mediators (regression coefficient β) on changes in the outcome variables. The significance of the product of the regression coefficients α and β (representing the mediated effect of the intervention) will be tested using bias-corrected bootstrap methods as outlined by Pituch and colleagues [87].

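### The primary aim compares with usual practice, but the contrasts named for PA and sedentary outcomes are factorial margins that shrink if the programmes do not add, and the stated 0.8 power holds only for those margins

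*Protocol article*

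**What the plan says.** - **Aims:** the question is whether the intervention "results in higher levels of physical activity and lower rates of sedentary behavior among 8-9 year old children compared with usual practice".
- **Data analysis, named contrasts:** "For physical activity outcomes, we will compare the PA-I and SB+PA-I versus the SB-I and C groups". Sedentary outcomes get the mirror contrast. A comparison with the control group alone is named only for health outcomes.
- **Data analysis, model:** the PA-I and SB-I conditions are the predictors of main interest, "entered in the form of two indicator variables and their interaction term".
- **Development and Pilot Phase:** the pilot of 2-minute class breaks found less sedentary time in class and "a corresponding 20-minute increase in moderate- to vigorous-intensity physical activity". No time unit is given.
- **Interrupting classroom sitting time (SB-I):** each two-hour teaching block is "interrupted every 30 minutes with a 2-minute guided light-intensity activity break". With two blocks a day, "this should result in up to 60-minutes less sitting time per week".
- **Combined arm section:** these schools "will receive a blended version of the two interventions, but with the same intervention 'dose". Table 2 gives this arm the same standing lessons and 2-minute breaks as SB-I.
- **Sample size calculations:** a standardized difference of 0.32, equated with "a mean change in objectively-measured PA of 8 minutes per day" (SD 18 min), is to be detected with 0.8 power for the two programmes singly and combined. This needs 340 children without clustering and 520 with an ICC of 0.018; 600 will be recruited.

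**The concern.** Three of the four arms are active, and in the PA contrast one of them, SB-I, sits on the comparator side. That is harmless if the SB programme adds the same amount of PA with or without the PA programme, because it then appears on both sides and cancels. If the combined arm gains less than the sum of the two single effects, the margin understates what PA-I does against usual practice.

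The document gives reasons to expect some shortfall. Its pilot suggests that SB-I may raise PA, and the combined arm divides the same number of lessons and newsletters between two behaviours. All three programmes could then beat usual practice while the one PA contrast that is named has a poor chance of showing it. The sample size section offers no warning, because its power statement does not distinguish a margin from an arm against control.

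**Working it through.** **Inputs.** From Sample size calculations: standardized difference 0.32, 8 min/day, SD 18, two-sided 0.05, power 0.8, retention 91%, ICC 0.018, 20 schools, 30 per school. The stated pair 8 and 18 gives 8/18 = 0.44, not 0.32; the SD that matches 0.32 is 8/0.32 = 25. Both SDs are carried below. The effects of SB-I and of the combined arm on PA are assumptions, since the document gives no daily figure for either.

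**The plan's own figures.** n per side = 2(1.96 + 0.842)²/0.32² = 154 after rounding up, so 308 in total. 308/0.91 = 339, or 17 × 20 = 340. With design effect 1 + 29 × 0.018 = 1.522: 308 × 1.522/0.91 = 515, or 26 × 20 = 520. Both stated figures reproduce, as a comparison of one half of the sample with the other half, which is a factorial margin.

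**The margin.** Let the effects on PA against control be a (PA-I), b (SB-I) and c (combined). Then

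PA margin = (a + c)/2 − (b + 0)/2 = (a + c − b)/2 = a + (c − a − b)/2.

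It equals a only if c = a + b. It is zero only if c = b − a, which for a > 0 means a combined arm worse than SB-I alone.

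**Precision at 600 recruited.** Retained 546, or 27.3 per school. Design effect 1 + 26.3 × 0.018 = 1.473. Effective n per side: 273/1.473 = 185 for a margin and 92.6 for one arm. Standard error in SD units: √(2/185) = 0.104 for a margin and √(2/92.6) = 0.147 for one arm against control. Power = Φ(difference/SE − 1.96).

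| Case (a = 8 min) | Contrast | Power, SD 25 | Power, SD 18 |
|---|---|---|---|
| Additive, any b | margin 8 | 0.87 | 0.99 |
| c = better single arm, b = 4 | margin 6 | 0.64 | 0.89 |
| c = better single arm, b = 8, 12 or 20 | margin 4 | 0.34 | 0.57 |
| c = mean of single arms, b = 12 | margin 3 | 0.21 | 0.36 |
| c = mean of single arms, b = 20 | margin 1 | 0.06 | 0.08 |
| PA-I against control | 8 | 0.59 | 0.86 |

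In the third row every active arm gains at least 8 min over control, yet the margin is 4, because (8 + b − b)/2 = 4 for any b of 8 or more. In the fourth and fifth rows the combined arm (10 and 14 min) does worse than SB-I alone (12 and 20 min).

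**Limits.** These are normal approximations with no allowance for the small number of schools or for any gain from baseline adjustment.

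**The case against.** Pooling over the other factor is the standard analysis of a 2 × 2 factorial, and the sample size was evidently built on it. SB-I on the comparator side is not a bias under additivity. The planned model has both indicators and their interaction, so with ordinary 0/1 coding it already yields PA-I against control, SB-I against control and the departure from additivity. The class breaks and standing lessons are listed at full frequency in the combined arm; only lessons, homework and newsletters are blended. All of this stands, so it would be wrong to say that the SB effect on PA cannot be estimated.

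A reader might also infer that SB-I is expected to add 20 min of MVPA a day, 2.5 times the planned PA effect, and that the PA margin could therefore be near zero. The documents do not support this. The pilot figure has no time unit. The trial's own breaks are light intensity and total 3 × 2 min × 2 blocks = 12 min a day. A near-zero margin would need a combined arm that does worse than SB-I alone despite having the same breaks and the PA components as well. The pilot is evidence of spill-over, not a forecast of its size.

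What the objection does not settle is which estimate answers the primary aim. Under 0/1 coding the indicator coefficients are effects against control, the named contrasts are margins, and the article does not choose between them. Nor does it explain the single 0.8.

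**Conclusion.** The point holds as a mismatch between aim, named contrasts and stated power, not as a bias. The adverse case that the documents make plausible is a halved PA margin: 4 min in place of 8, with power about 0.34 at SD 25 or 0.57 at SD 18, against 0.87 or 0.99 if effects add. It rests on two assumptions: SB-I alone raises PA by at least 8 min/day, and the combined arm gains nothing beyond the better single arm. With a smaller spill-over of 4 min the margin is 6 and power 0.64 (0.89). The algebra applies equally to the sedentary contrast.

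The power statement needs correcting whether or not effects add. The 0.8 reproduces only for a half-against-half margin; one arm against control at 8 min has about 0.59 (0.86 at SD 18).

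**What to change.** 1. State which contrast is primary for PA and for sedentary outcomes: the factorial margin or the arm-against-control effect.
2. From the model already planned, report for each of these outcomes both factor margins, the interaction, and each active arm against control, all with confidence intervals.
3. State that a null margin alone will not be read as no effect compared with usual practice.
4. Restate the 0.8 power as applying to the margins, and give the lower power for one arm against control, with the SD used.

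This changes wording and reporting only; arms, content and data collection stay as they are. The cost is more reported estimates and a less favourable stated power for the arm-level contrasts.

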### Theoretical basis of Transform-Us!

Physical activity interventions that base their strategies on behavioral theories are more likely to be effective than atheoretical approaches [51]. Table 1 shows the mediators that will be targeted in Transform-Us!. These mediators are based on elements of the behavioral theories that have previously been shown to be effective in encouraging behavior change in children's physical activity and sedentary behavior [44,51-54] including: social cognitive theory [26]; behavioral choice theory [28] and ecological systems theory [20]. These theories recognize that there are multiple levels of influence on health behavior including intrapersonal (e.g., awareness, self-efficacy, enjoyment), interpersonal (e.g., parents, siblings, peers, teachers), physical environmental (e.g., television in child's bedroom, access to parks/playgrounds), and policy influences (e.g., school physical activity policies and timetables). As previous research has shown consistent sex differences in physical activity [55] and in some sedentary behaviors (particularly computer use and playing electronic games [56-58]) and sex was a significant moderator in the Switch-Play study [44] the intervention will be tailored for boys and girls wherever possible. See Table 2 for a summary of the intervention strategies.

**Table 1 T1:** Theoretical* basis of the Transform-Us! intervention and links to program objectives

Constructs	Mediators or determinants	Program Objectives
Intrapersonal		
Confidence	Self-efficacy	Improve confidence in ability to be active or reduce sedentary time
Preference	Enjoyment	Increase enjoyment and preference for physical activity
Expectations	Benefits/barriers	Increase knowledge of benefits & strategies to overcome barriers
Expectancies	Evaluation of anticipated outcome	Alter perception of pros and cons of being more active
Skills	Self-management	Self-rewards, self instructions, TV viewing styles
Behavioral rehearsal	Self-monitoring & contracting	Goal setting, contracting with others, rewards
Interpersonal		
Observational learning	Modelling by parents/siblings	Encourage parents & siblings to reduce their own SB & increase PA
Social support	Modelling/social support	Encourage parents & siblings to support child to spend less time in SB & more time in PA; teachers encourage/support PA during recess/lunch
Social structure	Rules	Parents enforce rules regarding limiting screen time at home, during meals, during daylight hours
Environmental		
Imposed environment	Availability	Increase the amount of PA equipment available at school & home. Reduce the availability of TVs/computers/electronic games at home
Imposed environment	Access	Increase access/opportunities for PA at school & at home. Decrease access to TV/computers/electronic games at home
Imposed environment	Policy	Interrupted sitting during class-time; presence of supervising teachers during recess/lunch

* Based on social cognitive theory [26], behavioral choice theory [28], ecological systems theory [20]

**Table 2 T2:** Transform-Us! intervention components

	SB-I	PA-I	SB+PA-I
**School setting**			

Curriculum component	• 18 key learning messages (9 per year)	• 18 key learning messages (9 per year)	• 18 key learning messages (9 per year)
Class strategies	• Standing lessons (1 × 30-min/day) • Active 2- min breaks after 30-min class time	NA	• Standing lessons (1 × 30-min/day) • Active 2- min breaks after 30-min class time
Physical environment	• Standing easels • Novelty timer	• Provision of sporting equipment, line markings and signage • Provision of pedometers	• Standing easels • Provision of sporting equipment, line markings and signage • Provision of pedometers

**Family setting**			

Homework tasks	• Reduce sitting time while completing home work	• Homework tasks incorporate PA	• Homework tasks incorporate PA and reductions in sitting time
Newsletters	• Tips for reducing sitting time at home	• Tips for increasing PA at home	• Tips to reduce sitting time and promote PA at home

PA: physical activity; SB: sedentary behavior; PA-I: physical activity intervention; SB-I: sedentary behavior intervention

### Sedentary behavior intervention arm (SB-I)

Reducing uninterrupted time spent sitting during school hours will be aimed for in the school setting; and reducing overall sitting time and discretionary screen-based behaviors (i.e., television viewing, computer use and electronic games) will be aimed for in the family setting. In addition, key mediators of sedentary behavior change will be targeted (Table 1).

### School setting

#### Curriculum-based key learning messages

Key learning messages will be adapted from Switch-Play materials incorporating key principles of behavior change and delivered by classroom teachers in 18 lessons (9 lessons per year). Teachers will be provided with complete lesson plans but encouraged to modify the materials to suit their class and teaching style. The second year of the intervention will reinforce and enhance the lessons from the first year. Key messages will focus on raising awareness; self-monitoring; goal setting; behavioral contracts; social support (team-based activities at school; homework to do with parents); and feedback and reinforcement (external and intrinsic rewards). All lessons are developed in line with the Victorian Essential Learning Standards for year levels 3 and 4. Furthermore, children will be encouraged to meet the national recommendations for young people of less than two hours per day in electronic entertainment media [59].

#### Interrupting classroom sitting time

Teachers will modify the delivery of one class lesson per day (~30 minutes) so that children will complete the lesson standing up. Teachers will be provided with a suite of standing lesson delivery methods that can be modified to any class topic (e.g., 'Stations around the room' shown in Appendix 1). If administered as intended, this should result in approximately 150-minutes less sitting time per week. In addition, every two-hour classroom teaching block will be interrupted every 30 minutes with a 2-minute guided light-intensity activity break (e.g., 'Bean-bag Spelling/counting' shown in Appendix 2). This will equate to a total of six minutes interrupted sitting time every two hours. On average, schools in Victoria have two 2-hour teaching blocks per day so this should result in up to 60-minutes less sitting time per week. Teachers will be provided with a menu of activities to deliver during the 2-minute breaks.

#### Environmental cues and prompts

Each class will be provided with several standing easels so that children can rotate learning activities at 'standing stations'. In addition, a novelty timer will be given to each class so that teachers can monitor 2-minute standing breaks and every 30-minutes of sitting class time.

